#### 8.3.3.2 RELATIONSHIP TO STUDY INTERVENTION

Any of the above events can be considered Related or Unrelated. An event is Related if there is a reasonable possibility that the event may have been caused by or is linked in a significant way to the research. This encompasses all aspects of the research—it is not limited to test agents or procedures.

Unrelated (clearly not related to the research)

Unlikely (doubtfully related to the research)

Probable (likely related to the research)

Definite (clearly related to the research)

---

#### 8.3.3.3 EXPECTEDNESS

Unexpected Adverse Event: An unexpected adverse event is an adverse reaction, the nature or severity of which is not consistent with the applicable product information (e.g., package insert/summary of product characteristics for an approved product or device).

---

#### 8.3.4 TIME PERIOD AND FREQUENCY FOR EVENT ASSESSMENT AND FOLLOW-UP

The follow up plan for AEs will be AE-specific and so is the duration of the follow-up.

---

#### 8.3.5 ADVERSE EVENT REPORTING

The PI(s) at each site are responsible for making determinations regarding adverse events with respect to severity and/or attribution. However all members of the research team are responsible for reporting possible AEs to the PIs. All adverse events and unexpected adverse events should be reported to the clinical site's IRB per institutional standards. Adverse events will be reported to the coordinating center upon request to facilitate semi-annual reporting to NIAMS and the DSMB (through KAI).

---

#### 8.3.6 SERIOUS ADVERSE EVENT REPORTING

The PI(s) at each site are responsible for making determinations regarding adverse events with respect to severity and/or attribution. However all members of the research team are responsible for reporting possible AEs to the PIs. Serious adverse events should be reported to the coordinating center. Clinical sites will also report events to their IRB, per institutional standards. The coordinating center will report events to University of Michigan IRBMED, NIAMS and the DSMB (through the executive secretary, KAI research, Inc.) within 48 hours of the investigator becoming aware of the event.

---

#### 8.3.7 REPORTING EVENTS TO PARTICIPANTS

Not applicable.

---

#### 8.3.8 EVENTS OF SPECIAL INTEREST

Not applicable.

### 8.3.9 REPORTING OF PREGNANCY

Not applicable.

## 9 STATISTICAL CONSIDERATIONS

### 9.1 STATISTICAL HYPOTHESES

**Aim 1:** To compare 24-month post-surgical outcomes of elderly DRFs treated with VLPS with CRP and EFP.

*Rationale:* Internal fixation allows for earlier motion of the affected hand and wrist, which prevents complications related to immobilization and potentially results in better functional outcomes.

*Hypothesis:* Patients treated with VLPS will have better outcomes than those treated with CRP and EFP.

**Aim 2:** To compare the recovery trend for elderly DRFs treated with VLPS with CRP and EFP.

*Rationale:* The rate of recovery for these three treatment methods is unknown. Patients will be assessed at 2 weeks, 6 weeks, 3 months, 6 months, 12 months and 24 months after surgical treatment to determine which treatment method provides the most rapid recovery.

*Hypothesis:* Patients treated with VLPS will have better outcomes at earlier times than those treated with the more conservative techniques, and the better outcomes will persist at the 24-month period.

**Aim 3:** To determine predictors of outcomes after surgical treatment of DRFs in the elderly.

*Rationale:* Predictors of functional outcomes in the elderly have not been studied. We will evaluate predictors of outcomes based on demographic characteristics, fracture patterns and treatment types.

*Hypothesis:* Severity of fracture, adequacy of reduction, bone mineral density, preinjury functional status and patient socioeconomic status are predictors of functional outcomes after treatment.

**Aim 4:** To compare the 12-month post-surgical outcomes and 24-month recovery trends of patients who have chosen not to have surgery with patients within the surgical arm.

*Rationale:* Elderly patients may have low functional demands, and it has been postulated that they can tolerate the deformity that almost certainly results following treatment with closed reduction and casting only.

*Hypothesis:* Patients treated with surgery will have better outcomes earlier than those treated nonsurgically.

**Aim 5:** To conduct a cost-utility analysis comparing the three treatment arms with the nonsurgical arm.

*Rationale:* A formal economic analysis comparing the three treatment options for DRFs has not been performed. We will evaluate cost and patient preferences to arrive at a dominant strategy.

*Hypothesis:* Although VLPS is more costly, earlier functional gains makes this treatment a dominant strategy.

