| Study Description:                                      | The goal of this 24-center randomized controlled trial is to compare the physical, functional and quality of life outcomes of three different surgical methods for treating distal radius fractures in the elderly: close reduction and percutaneous pinning (CRPP), external fixation with or without percutaneous pinning (EFP) and internal fixation with volar locking plates. We will also follow a cohort of patients who opt for the non-surgical treatment, close reduction and casting, to examine and compare the same outcomes following non-surgical treatment. |
| Objectives:                                             | 
Primary Objective: To compare outcomes of DRFs in patients age 60 years and older treated with VLPS with those treated with EFP, CRPP, and casting
 
Secondary Objectives: to compare the trend of recovery for DRFs treated with VLPS with the other fixation techniques and to determine predictors of outcomes
                                                                                                                                                                                                                                               |
| Endpoints:                                              | 
Primary Endpoint: Michigan Hand Outcomes Questionnaire Summary score at 12-month assessment
 
Secondary Endpoints: Michigan Hand Outcomes Questionnaire Subdomain scores, SF-36, RAPA, hand strength, wrist range of motion
                                                                                                                                                                                                                                                                                                                                     |
| Study Population:                                       | Community-dwelling adults age 60 years or older presenting to participating sites' emergency or urgent care department with isolated closed distal radius fracture                                                                                                                                                                                                                                                                                                                                                                                                          |

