### 3 OBJECTIVES AND ENDPOINTS

| OBJECTIVES                                                                                                                                                                                                                        | ENDPOINTS                                                                                       | JUSTIFICATION FOR ENDPOINTS                                                                                                                          |
|-----------------------------------------------------------------------------------------------------------------------------------------------------------------------------------------------------------------------------------|-------------------------------------------------------------------------------------------------|------------------------------------------------------------------------------------------------------------------------------------------------------|
| Primary                                                                                                                                                                                                                    |                                                                                                 |                                                                                                                                                      |
| To compare outcomes of DRFs in patients age 60 years and older treated with VLPS with those treated with EFP, CRPP, and casting                                                                                                   | Michigan Hand Outcomes Questionnaire (MHQ) Summary score at 12-month assessment                 | The MHQ is a legacy questionnaire for assessment of hand and wrist health                                                                            |
| Secondary                                                                                                                                                                                                                  |                                                                                                 |                                                                                                                                                      |

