## 9.2 SAMPLE SIZE DETERMINATION

We propose to randomize 474 patients to one of three surgical arms (158 per surgical arm). We will follow another 158 non-surgical patients meeting the inclusion/exclusion criteria. Sample size was determined to have adequate power for Aim 1 based on the primary outcome of the MHQ summary score at 12-month follow-up. **We expect to have complete data for 12-month follow-up time from 126 patients in each group, after accounting for a conservatively estimated 20% decrease in sample size from losses to follow-up.** For Aim 1, we expect 126 patients per group to give 80% power to detect an 8 point difference in the mean MHQ summary scores between VLPS and CRP and between VLPS and EFP using a mixed-effects model with a two-sided 0.025  $\alpha$ -level test. This assumes a standard deviation (SD) of 18 points (corresponding to an effect size of 0.44 SD), an average of 24 patients per site and an intra-site correlation coefficient (ICC) of 0.012. **To adjust for potential within surgeon correlation, we will also consider either a three level hierarchical model with surgeons nested within site, or use surgeons instead of sites as random intercepts. If technical variation is mostly between surgeons, addressing within surgeon correlation will reduce the ICC, which would give larger power to detect the same effect size. Covariate adjustments will likely give greater power by reducing the variability when the covariates are associated with the outcome and are not highly correlated with other covariates in the model.** We expect the 8 point difference in MHQ score at 12-months as a minimally detectable and meaningful difference between VLPS and either CRP or EFP. Our retrospective study of patients treated with VLPS showed mean ( $\pm$ SD) MHQ scores of 77 ( $\pm$ 15) at 3 months, 81 ( $\pm$ 17) at 6 months, and 85 ( $\pm$ 18) at 12 months for elderly patients. We believe the observed improvement of 8 points from 3 to 12 months to be similar to the expected post-surgical improvement difference between VLPS surgery compared with either EFP or CRP.

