### 9.4.2 ANALYSIS OF THE PRIMARY EFFICACY ENDPOINT(S)

**Aim 1:** *To compare 12-month post-surgical outcomes of elderly DRFs treated with VLPS with CRP and EFP.* Primary outcome will be the summary score of the MHQ. We will report means for each group and the mean difference between pairs of each group, along with their 95% confidence intervals. The primary outcome will be compared using a linear mixed-effects model to address the hierarchical nature of the data. The model will include surgeons nested within site and sites as random effects, fracture severity group indicator effect and two indicators for EFP and CRP groups. The surgical procedure indicators will each estimate the difference between EFP to VLPS and CRP to VLPS. We will also obtain covariate adjusted estimates of the between group differences; the covariates will be determined by the baseline analyses and will likely include age, baseline MHQ score, dominance of the injured hand and baseline RAPA score. Similar analyses will be done using other secondary outcome variables, including grip strength. We will also calculate MHQ score and grip strength as the difference (and %) of the uninjured hand scores. These measures may better reflect recovery because the uninjured hand can give a proxy measure of the patient-specific maximum achievable outcome. Analysis of complications will depend on how often they occur. For example, if the combined complications are rare, we will dichotomize them as present/absent and use a generalized linear mixed-effects model with logit link to compare the odds of complication between VLPS/EFP and between VLPS/CRP, while adjusting for within surgeon and site correlation. If the number of complications is substantial, we will use a count data model such as generalized linear model with log link to make the between-group comparison.

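### Aim 1 is titled a 24-month comparison in two sections although its endpoint, power and analysis are all at 12 months, and its 95% intervals do not match the planned 0.025 tests

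*Protocol*

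**What the plan says.** **Time point.** The Aim 1 title in Section 9.1, repeated in Section 4.1, reads "To compare 24-month post-surgical outcomes of elderly DRFs treated with VLPS with CRP and EFP". Section 9.4.2 restates the aim as "To compare 12-month post-surgical outcomes of elderly DRFs treated with VLPS with CRP and EFP". The synopsis gives "Primary Endpoint: Michigan Hand Outcomes Questionnaire Summary score at 12-month assessment", Section 3 gives "Michigan Hand Outcomes Questionnaire (MHQ) Summary score at 12-month assessment", and Section 9.2 says "Sample size was determined to have adequate power for Aim 1 based on the primary outcome of the MHQ summary score at 12-month follow-up". The hypothesis line under Aim 1 names no time point: "Patients treated with VLPS will have better outcomes than those treated with CRP and EFP". Within Section 9.4.2, the Aim 2 text already plans a comparison of outcomes at 24 months. The schedule of activities collects the full MHQ at both visits.

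**Test level and intervals.** Section 9.2 powers the contrast of VLPS with CRP and the contrast "between VLPS and EFP using a mixed-effects model with a two-sided 0.025" level for each. Section 9.4.2 plans to report group means and "the mean difference between pairs of each group, along with their 95% confidence intervals". It then names the mixed-effects model for the comparison, without repeating the test level.

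**The concern.** The section headed Statistical Hypotheses is where a reader looks for the primary claim, and there the aim carries a time point that differs from the primary endpoint. Both results will exist. Someone citing Section 9.1 could dispute a 12-month claim, or present a 24-month result as answering Aim 1, although the trial was not sized for that contrast. With Section 9.1 as worded, the 24-month contrast belongs to both Aim 1 and Aim 2.

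The interval level raises a smaller question. A 95% interval corresponds to a two-sided 0.05 test, but each of the two primary contrasts is planned at 0.025. For a band of observed differences, the reported interval and the planned test would point in opposite directions, and the report would have to explain why.

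**Working it through.** **Inputs, all from Section 9.2 unless stated.** Difference 8 points; SD 18; two-sided alpha 0.025 for each of two contrasts; power 80%; 24 patients per site; ICC 0.012; 158 randomized per arm; 20% loss; 126 evaluable per group. The 95% interval level is from Section 9.4.2.

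**1. Reproduce the plan's sample size at 12 months.**
- Unclustered n per group = 2 × [18 × (2.241 + 0.842) / 8]² = 96.2, rounded up to 97.
- Design effect = 1 + (24 − 1) × 0.012 = 1.276.
- 97 × 1.276 = 123.8, so 124. The t-based version gives 98 × 1.276 = 125.0. The rounded effect size of 0.44 SD gives 99 × 1.276 = 126.3.
- Power with 126 per group is 0.811 (normal) or 0.805 (t).
- 158 × 0.80 = 126.4 evaluable.

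The plan's 126 and 80% therefore reproduce at 12 months and 0.025 per contrast.

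**2. What a 24-month Aim 1 would rest on.** Section 9.2 gives power for slopes and for time-averaged differences, but none for a difference in means at 24 months and no loss rate for that visit. Taking 24-month loss as an assumption and keeping every other input:

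| Assumed loss at 24 months | Evaluable per arm | Power for 8 points at 0.025 |
|---|---|---|
| 20% | 126.4 | 0.81 |
| 25% | 118.5 | 0.78 |
| 30% | 110.6 | 0.75 |
| 40% | 94.8 | 0.68 |

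**3. Interval against test.**
- SE of a pairwise difference = 18 × √(2 × 1.276 / 126) = 2.56 points.
- 95% half-width = 1.960 × 2.56 = 5.02 points.
- 97.5% half-width = 2.241 × 2.56 = 5.74 points.
- Ratio = 2.241 / 1.960 = 1.14.

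An observed difference between about 5.0 and 5.7 points excludes zero at 95% but is not significant at 0.025.

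**4. Error control as designed.** Two tests at 0.025 sum to at most 0.05. With correlation 0.5 between the contrasts, from the shared VLPS arm and equal allocation, the family-wise error is 0.046.

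**The case against.** The strongest reply is that the plan already has one primary time point and one test level. Every place that designates, powers or analyses the primary endpoint says 12 months. The words at 24 months stand only in an aim title, refer to outcomes in general and are not tied to the MHQ. The Aim 1 hypothesis line gives no month, and Aim 2 already houses the 24-month comparison. On the error rate, 0.025 is the only level stated for the VLPS contrasts. The 95% intervals cover arm means and all pairs, including EFP with CRP, so they read as description. The test level in the analysis section could also be left to a statistical analysis plan that is not at hand.

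Most of this stands. A reader might infer that the primary claim has no fixed time point or error rate and that error control is lost. The documents do not support that. Deciding by 95% intervals at 12 months would give a family-wise error of about 9.1% for the two VLPS contrasts. Taking the better of the two visits at 0.025 would give about 7.4% to 9.0%, and doing both about 14% to 17%, for assumed between-visit correlations of 0.8 down to 0.2. But the protocol contains neither rule.

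What the reply does not remove is that the protocol states two different months for the same aim, one of them in its formal hypotheses section. No unseen document is needed to see that conflict. The reply also leaves the primary contrasts reported at a level that differs from their test.

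**Conclusion.** The point holds as a consistency correction, not as a defect in the design. The Aim 1 title in Sections 4.1 and 9.1 conflicts with the 12-month endpoint, sample size and analysis, and the sample size calculation supports only the 12-month reading. The 95% intervals differ from the planned 0.025 tests, which matters for observed differences of about 5.0 to 5.7 points.

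That band rests on the plan's SD of 18, its design effect of 1.276 and 126 evaluable per group. Another standard error would move both limits in proportion and leave the 1.14 ratio unchanged. The 24-month power figures depend on assumed loss rates and only illustrate that no such power is stated.

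**What to change.** - In Sections 4.1 and 9.1, change the month in the Aim 1 title to 12. Leave the 24-month comparison under Aim 2, where Section 9.4.2 already has it.
- In Section 9.4.2, state that VLPS against CRP and VLPS against EFP are each tested at two-sided 0.025. Then either report 97.5% intervals for these two contrasts, or keep the 95% intervals and label them descriptive.
- Do not pair a Holm procedure with fixed 97.5% intervals. Holm may test the second contrast at 0.05, so it could reject while the 97.5% interval still includes zero.

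The cost is a few words in three sections and, if 97.5% intervals are chosen, two intervals about 14% wider. Sample size, visits and data collection stay as they are.

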## 9.2 SAMPLE SIZE DETERMINATION

We propose to randomize 474 patients to one of three surgical arms (158 per surgical arm). We will follow another 158 non-surgical patients meeting the inclusion/exclusion criteria. Sample size was determined to have adequate power for Aim 1 based on the primary outcome of the MHQ summary score at 12-month follow-up. **We expect to have complete data for 12-month follow-up time from 126 patients in each group, after accounting for a conservatively estimated 20% decrease in sample size from losses to follow-up.** For Aim 1, we expect 126 patients per group to give 80% power to detect an 8 point difference in the mean MHQ summary scores between VLPS and CRP and between VLPS and EFP using a mixed-effects model with a two-sided 0.025  $\alpha$ -level test. This assumes a standard deviation (SD) of 18 points (corresponding to an effect size of 0.44 SD), an average of 24 patients per site and an intra-site correlation coefficient (ICC) of 0.012. **To adjust for potential within surgeon correlation, we will also consider either a three level hierarchical model with surgeons nested within site, or use surgeons instead of sites as random intercepts. If technical variation is mostly between surgeons, addressing within surgeon correlation will reduce the ICC, which would give larger power to detect the same effect size. Covariate adjustments will likely give greater power by reducing the variability when the covariates are associated with the outcome and are not highly correlated with other covariates in the model.** We expect the 8 point difference in MHQ score at 12-months as a minimally detectable and meaningful difference between VLPS and either CRP or EFP. Our retrospective study of patients treated with VLPS showed mean ( $\pm$ SD) MHQ scores of 77 ( $\pm$ 15) at 3 months, 81 ( $\pm$ 17) at 6 months, and 85 ( $\pm$ 18) at 12 months for elderly patients. We believe the observed improvement of 8 points from 3 to 12 months to be similar to the expected post-surgical improvement difference between VLPS surgery compared with either EFP or CRP.

For Aim 2, the proposed sample size and longitudinally assessed outcomes will provide 80% power to detect a between-group difference in the monthly rates of improvement of 0.22 points or greater with an  $\alpha$  level of 0.025, assuming a within-person correlation of 0.2 and ICC of 0.012. **For Aim 3, we consider power for a hypothetical scenario in which VLPS effect is smallest in the least active and largest in the most active patients. The study will have 83% power to detect the difference in the effect sizes for the VLPS to CRP group of 0.05 SD in the lowest, 0.30 SD in the moderate and 1.0 SD in the highest activity subgroups based on a 2 by 3 two-way analysis of variance, assuming about even number of patients in the three baseline activity subgroups. We note that though we do not hypothesize a differential effect of treatment in any subgroup, we will have adequate power to detect a differential treatment effect as large or larger than the hypothesized scenario, and the study will have adequate power to detect predictor effects that are homogeneous across subgroups as long as the predictor effects are as large as the effect size associated with the surgical procedures.** Aim 4 will compare outcomes between the combined surgical groups versus non-surgical group in which we expect the difference to be larger than the differences between VLPS and either EFP or CRP. We therefore expect the statistical power using the proposed number of non-surgical group patients to be more than adequate to make this comparison.

As described in Section C11 under Aim 1, a small portion of patients may cross over intra-operatively from a randomly assigned procedure of EFP or CRP to VLPS. Whether the analysis is done using intent-to-treat or as-treated, such cross-over cases may result in somewhat smaller effect sizes than when there were no cross-over cases. Nonetheless, having outcomes measured longitudinally over a 24-month period gives the study adequate power to detect a time-averaged difference between two surgical arms much smaller than the difference based only at 12 months. Specifically, the proposed study gives 80% power to detect a time-averaged difference as small as 4.8 points, using a 0.025 level two-sided test based on mixed-effects model with three follow-up assessments and assuming an SD of 18 and a within-person correlation of 0.2. In addition, using the as-treated analysis, in a worst case scenario in which 10% of both EFP and CRP patients cross over to VLPS, sample size will not be equal across the three groups. This, however, will not affect the power significantly. Specifically, we will still have 80% power to detect a time-averaged difference in the MHQ scores of about 5 points between EFP or CRP (N = 113 per group) to VLPS (N = 152) with 0.025 level test. The power calculations were done using NQuery Advisor 7.0 (Saugus, MA), with appropriate considerations for longitudinally measured data.

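### The stated 80% power is per contrast, not for beating both comparators, and the fixed 0.025 split is dominated by Holm's procedure at no extra sample size

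*Protocol*

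**What the plan says.** Protocol section 9.1 gives Aim 1 a single hypothesis: "Patients treated with VLPS will have better outcomes than those treated with CRP and EFP". Section 4.1 repeats it.

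Section 9.2 sizes the trial on the 12-month MHQ summary score. It claims "80% power to detect an 8 point difference in the mean MHQ summary scores between VLPS and CRP and between VLPS and EFP". Each contrast is to be tested at a two-sided level of 0.025. The remaining inputs are an SD of 18, which makes the 8 points 0.44 SD, and 126 evaluable patients per arm out of 158 randomised. For clustering it takes "an average of 24 patients per site and an intra-site correlation coefficient (ICC) of 0.012". The 8 points are described as a "minimally detectable and meaningful difference between VLPS and either CRP or EFP".

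Section 9.4.2 fits one mixed model with two treatment indicators: "The surgical procedure indicators will each estimate the difference between EFP to VLPS and CRP to VLPS". It plans 95% confidence intervals and does not repeat the 0.025 level. Neither section explains why 0.025 was chosen. That it is 0.05 shared between two contrasts is an inference.

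**The concern.** Two things are at stake.

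- **What the 80% refers to.** A hypothesis naming both comparators can be read as a joint claim. The chance that both contrasts succeed is lower than the chance that a given one does, so a reader who takes 80% as the power for the sentence in 9.1 will be misled.
- **Whether the fixed 0.025 is a good choice.** Once one contrast has been rejected at 0.025, the other can be tested at 0.05 without breaking family-wise control. A fixed split holds the second contrast to 0.025 regardless and so gives up power.

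**Working it through.** **Inputs.** Section 9.2 gives a difference of 8 for each contrast, SD 18, 126 evaluable per arm, two-sided 0.025, 24 patients per site and ICC 0.012. Section 6.3 says randomisation is stratified by site. Assumption: both true differences are 8 points.

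**1. Reproduce the stated 80%.**
- Design effect: 1 + 23 × 0.012 = 1.276.
- SE of one contrast: 18 × √(2 × 1.276 / 126) = 2.562.
- Standardised difference: 8 / 2.562 = 3.123.
- Power at two-sided 0.025: Φ(3.123 − 2.241) = 81.1% (80.5% by noncentral t).
- Reverse check: 97 per arm without clustering × 1.276 = 124, against 126 planned; 158 × 0.8 = 126.4.

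The stated figure is therefore sound, and it belongs to one contrast. Without the design effect, one contrast would have 90.1%.

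**2. Joint power under the fixed split.** Each contrast has variance 2σ²/n. Their covariance is σ²/n, from the shared VLPS arm, so the correlation is 0.5 with equal arms. The probability that both pass is the bivariate normal probability Φ₂(z − 2.241, z − 2.241; 0.5):
- 68.7% if each contrast has exactly 80% (67.6% to 69.9% for correlations of 0.4 to 0.6);
- 70.2% at z = 3.123;
- 83.4% without the design effect (SE 2.268, z = 3.528).

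At z = 3.123, at least one passes in 2 × 81.1 − 70.2 = 92.0% of trials, and exactly one in about 22%.

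**3. The same data under Holm.** Test the smaller p at 0.025 and, only if it is significant, the other at 0.05. Both are rejected when both p values are below 0.05 and at least one is below 0.025. The added joint rejections are trials in which one contrast passes 0.025 and the other lies between 0.025 and 0.05. By symmetry half of that gain goes to each contrast, so at z = 3.123 per-contrast power is 81.1 + (79.1 − 70.2)/2 = 85.5%.

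| Setting | Per contrast, split | Per contrast, Holm | Both, split | Both, Holm |
|---|---|---|---|---|
| Exactly 80% per contrast | 80.0% | 84.6% | 68.7% | 77.8% |
| Design effect 1.276 | 81.1% | 85.5% | 70.2% | 79.1% |
| No design effect | 90.1% | 93.1% | 83.4% | 89.5% |

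**4. Error control.** If both nulls are true, a false rejection needs the smaller p to be below 0.025, which has probability at most 2 × 0.025 = 0.05. If one null is true, falsely rejecting it needs its own p below 0.05. The family-wise error is therefore at most 0.05 in every case, the same bound as for the split.

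**The case against.** The strongest reply is that the protocol means two separate claims. Section 9.2 refers to VLPS against *either* comparator, and the indicators in 9.4.2 *each* estimate their own difference. The Aim 2 text there also hypothesises a negative effect for EFP and CRP each. On that reading, 0.025 per contrast and 80% per contrast are consistent. This stands, and it is the more natural reading of the analysis text.

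A reader might infer more: that the 80% is an error, that the trial is underpowered, or that the primary verdict is undefined in the roughly one trial in five where exactly one contrast passes. The documents do not support these. Section 9.2 never claims joint power, and no section sets a single pass/fail verdict. A lone significant contrast can simply be reported as such. The joint shortfall rests on the word *and* in the hypothesis.

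The design effect can also be challenged. With randomisation stratified by site, arms are compared within sites, so 69-70% is the cautious end and 83% the other.

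Finally, a fixed 0.025 is valid, and preferring a step-wise test could be called taste or left to the SAP. But 9.2 itself fixes the level, and Holm is never worse in what it rejects under either reading. Its real drawback is that matching simultaneous intervals are less simple than 97.5% intervals. The 95% intervals planned in 9.4.2 do not match a 0.025 test either.

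**Conclusion.** The stated 80% is a correct per-contrast figure and should be labelled as one. For the Aim 1 hypothesis read as a win over both comparators, power is about 69-70% with the protocol's design effect, or about 83% without it. This assumes true differences of 8 points on both contrasts and a correlation of 0.5.

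Independently of that reading, the fixed 0.025 split is dominated. Holm has the same family-wise bound of 0.05 and gains about 4 to 5 points of per-contrast power and about 9 points of joint power under the protocol's inputs. Without the design effect the gains are about 3 and 6 points. This is an avoidable loss of efficiency and an unclear label; it does not make the planned tests invalid.

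**What to change.** In sections 9.2 and 9.4.2:

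1. Replace the fixed 0.025 with Holm over the two 12-month contrasts at family-wise two-sided 0.05: smaller p at 0.025 and, only if significant, the other p at 0.05. Name Holm alone. Hochberg is a different rule: with p values of 0.03 and 0.04 it rejects both, and Holm rejects neither.
2. State that each rejection supports only its own contrast, and that VLPS is concluded to be better than both CRP and EFP only if both are rejected in favour of VLPS.
3. Label the 80% as per contrast. Give the joint power with its dependence on the design effect: about 70% (split) or 79% (Holm) with it, about 83% or 89.5% without.
4. State which confidence intervals accompany the tests.

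No patients or data are added. The costs are less simple matching intervals and a constraint on timing: the rule must be fixed before the outcome data are analysed. The latest version in section 10.3 is dated 04/03/18 and mentions manuscript submission. If the outcome data have already been analysed, the testing rule should stay as it is and only the labelling and interpretation in items 2 and 3 should be clarified.
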